### Participant timeline {13}

The participant timeline will consist of two visits and about 1 week of home dressing changes between them. The duration of participation is approximately 1 week after the study introduction. We anticipate participant recruitment to last 48 months. The timeline by intervention group and procedures is listed in Table 1 below.

**Table 1 Tab1:** Survey procedures and timing of study visits

	**Visit 1** (Enrollment)	**Home dressing changes** (~ 1 week)	**Visit 2** (~ 7 days after enrollment)
Baseline survey (*n* = 1)	X		
Randomization	X		
VR-PAT download and headset distribution	Intervention group		Control group
Child questionnaire (*n* = 7)		X	
Caregiver questionnaire (*n* = 7)		X	
Medication questionnaire (*n* = 7)		X	
Follow-up survey (*n* = 1)			X
Incentive distribution (at survey return)			X

### Sample size {14}

The sample size was calculated for the primary outcome of the child-reported overall pain score. We consider a 30% reduction in the pain NRS score as a minimal clinically meaningful reduction in pain. According to our previous publication on pain reduction of VR-PAT among pediatric patients 6–17 years of age who were treated at our outpatient burn clinic [19], the pooled standard deviation (SD) of the child-reported overall pain visual analog scale (VAS) score was estimated. Aiming at detecting a 30% reduction of the pain score in the VR-PAT group compared with the control group at any of the first 7 days of follow-up, and assuming the same SD on these days, we will need 89 subjects per group to achieve 80% power and a two-sided type-I error of 0.01 at each day using a two-sample *t*-test. The type-I error rate is adjusted by Bonferroni correction for multiple comparisons. Assuming a 10% dropout rate, we will need 99 subjects per group. Based on this calculation, we plan to *n* = 100 subjects per group (*n* = 200 subjects total).

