### Eligibility criteria {10}

Eligibility will be assessed using the following criteria: (a) undergoing treatment for acute burn injury; (b) age 6–17 years, inclusive; (c) receiving their first outpatient clinic dressing change or being discharged from the ED or inpatient burn unit; (d) having a dressing that requires daily changes at home for about 5 days after their first outpatient appointment or discharge from the hospital; (e) patient and family caregivers can communicate (read and write) using English or Spanish; and (f) report an NRS pain score of ≥ 1 (NRS 0–10 with 10 being worst pain) from the most recent dressing change. To minimize the possibility of confounding variables, the following exclusion criteria will be applied: (a) any wounds that may interfere with study procedures (i.e., face burns); (b) vision, hearing, or cognitive/motor impairments preventing valid administration of study measures; (c) history of motion sickness, seizure disorder, dizziness, or migraine headaches precipitated by visual auras; (d) minors in foster care, prisoners, or those who are currently pregnant; (e) suspected child abuse; (f) unable to communicate in English or Spanish; and (g) families who do not have access to a VR compatible smartphone.

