## Statistical methods

### Statistical methods for primary and secondary outcomes {20a}

#### Aim 1

In the primary analysis, the child-reported overall pain NRS score will be compared between the VR-PAT and control groups during each of the first 7 days of follow-up using a two-sample *t*-test. The *p* values will be adjusted by Bonferroni correction to account for multiple comparisons and then compared to the critical value of 0.05 to determine statistical significance. In the secondary analysis, child-reported worst pain score, parent-observed overall and worst pain scores, child engagement and experience with VR, caregiver report of VR use, and adverse effects related to engagement with VR will be compared between the two study groups using a two-sample *t*-test (for continuous variables) and chi-squared test (for categorical variables). To estimate the overall difference in the child-reported overall pain score between the two study groups over the 7 days of follow-up, a linear mixed effect model with random intercept accounting for the correlation among repeated measures of pain scores will be fit. The dependent variable of the model will be child-reported overall pain score. The independent variables of the model will contain the study group, time (follow-up days), and any potential confounders deemed unbalanced between the study groups. The coefficient of the study group is the estimated overall difference in the pain score. To further explore whether the trend of child-reported overall pain score over the 7 days differs between study groups, the same linear mixed effect model as above will be fit with the addition of interaction between the study group and time. The coefficient of the interaction term estimates the difference in the trend of pain scores over time.

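### The sample size states a per-day alpha of 0.01, but the planned Bonferroni correction over seven daily tests gives 0.0071; if 0.01 was used exactly, per-day power is about 77%, not 80%

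*Protocol article*

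**What the plan says.** The section Sample size {14} sets the target for the child-reported overall pain score. It aims to detect a 30% reduction "at any of the first 7 days of follow-up" and concludes: "we will need 89 subjects per group to achieve 80% power and a two-sided type-I error of 0.01 at each day", using a two-sample t-test. It then adds: "The type-I error rate is adjusted by Bonferroni correction for multiple comparisons". A 10% dropout allowance takes 89 to 99 per group, and 100 per group are planned.

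The section Statistical methods for primary and secondary outcomes {20a}, Aim 1, gives the matching primary analysis. The same score "will be compared between the VR-PAT and control groups during each of the first 7 days of follow-up" by two-sample t-test. The p values are Bonferroni-adjusted and then compared with 0.05.

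The 30% reduction is relative. The article says that a pooled standard deviation was estimated from an earlier outpatient trial, but prints neither that value nor the control mean to which the 30% applies.

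**The concern.** Both sections describe seven daily comparisons with a Bonferroni correction, so the per-day level should be 0.05/7 = 0.00714. The printed level is 0.01. Seven tests at 0.01 have a Bonferroni bound of 7 × 0.01 = 0.07, and a family-wise error of 1 − 0.99^7 = 0.068 if independent. The sample-size paragraph therefore does not agree with itself or with the analysis section.

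What is at stake is the stated 80% power. If the calculation was run at 0.01 and the tests will be judged at 0.00714, each daily test is stricter than the one the sample size was built for. A reader relying on 80% per day would then be relying on a figure that the planned analysis does not deliver.

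**Working it through.** **Inputs.** From Sample size {14}: 89 evaluable per group, 80% power, two-sided alpha 0.01 per day, two-sample t-test, 10% dropout, 100 per group planned. From Statistical methods {20a}: seven daily tests, with Bonferroni-adjusted p values compared with 0.05. From Trial design {8}: 1:1 allocation. Not given: standard deviation and control mean.

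**Step 1: the plan's own figures.** The dropout step reproduces: 89/0.9 = 98.9, rounded up to 99. The 89 itself cannot be rebuilt from the article, because the effect in standard-deviation units is not stated. It can only be solved backwards.

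**Step 2: implied effect if 0.01 was used exactly.** Normal approximation:

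d = (z₀.₉₉₅ + z₀.₈₀) × √(2/n) = (2.576 + 0.842) × √(2/89) = 3.417 × 0.1499 = 0.512.

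The noncentral t, which suits the planned test, gives d = 0.517.

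**Step 3: power at the level the analysis will use.** For two-sided 0.00714, z = 2.690. Normal approximation with 89 per group:

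power = Φ(3.417 − 2.690) = Φ(0.727) = 76.6%.

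Noncentral t with d = 0.517 and alpha 0.00714:

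| Evaluable per group | Per-day power |
|---|---|
| 89 | 76.6% |
| 90 (100 planned less 10%) | 77.2% |
| 100 (no dropout) | 82.5% |

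If 89 was itself rounded up from just over 88, d could be as high as 0.520. Power with 89 is then 77.2%, so the conclusion does not turn on rounding of n.

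**Step 4: size needed for 80% at 0.00714.** Normal approximation:

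n = 2 × (2.690 + 0.842)² / 0.512² ≈ 95.05, rounded up to 96.

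The noncentral t also gives 96 (95 at d = 0.520). With 10% dropout, 96/0.9 = 106.7, or 107 per group.

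**Step 5: the other reading.** Suppose that 89 was computed at 0.05/7 and the alpha was then printed to two decimals, since 0.00714 rounds to 0.01. The implied d is then 0.535 (noncentral t) and per-day power is 80%, as stated. With that effect, a true alpha of 0.01 would have needed only 84 per group, so the printed alpha would not lead to the printed 89.

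**Step 6: which reading holds.** The two readings need standardised effects of 0.517 and 0.535. The standard deviation and control mean would show which one was used, and the article prints neither.

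**The case against.** The strongest reply is that nothing is wrong beyond a rounded number. The sample-size paragraph names seven days and Bonferroni, so whoever wrote it may well have calculated at 0.00714 and printed two decimals. This stands as a possibility, and it is why the power loss can be stated only conditionally. It does not remove the point. Printing 0.01 for 0.00714 enlarges the level by 40%, enough to move the required size from 89 to 84 at the same effect, so the sentence needs correcting either way.

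A second reply is that the practical consequence is small. Much of this stands too. The shortfall on the literal reading is about 3 points, and power is above 80% if all 100 per group are evaluable. The figure of 77% is for one named day. If the same effect held on all seven days, the chance of at least one significant day would be higher: simulation at d = 0.517 with 89 per group gives from just under 90% to about 98% for assumed between-day correlations of 0.9 down to 0.5. But the article attaches its 80% to each day, so the per-day figure is the one to check.

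Two stronger readings are tempting and are not supported:

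- A reader might notice that 0.01 = 0.05/5 and that Eligibility criteria {10} asks for "having a dressing that requires daily changes at home for about 5 days", and infer that the trial was sized for five tests and is analysed with seven. No section defines a family of five comparisons; both relevant sections say seven days.
- A reader might infer that days 6 and 7 will be badly underpowered because some children will have finished their changes. The eligibility wording is an entry condition, not an expected duration. The Background mentions changes often lasting 2–3 weeks, Table 1 supplies seven questionnaires, and the child survey is planned for 7 days. Some thinning by day 7 is plausible, but the article gives no retention figure from which to calculate a power.

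**Conclusion.** The point holds in conditional form. The printed per-day alpha of 0.01 is not the Bonferroni level for the seven planned tests, which is 0.00714, so the stated alpha and power do not together describe the primary analysis.

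- If 0.01 was used exactly, per-day power is about 77% instead of 80%, a shortfall of 3.4 points at 89 per group.
- If the calculation used 0.00714, the 80% is right and only the printed alpha is wrong.

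The article cannot decide between these. Both results assume a two-sample t-test with equal groups and the same standardised effect each day, back-solved from the stated 89.

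A reader might infer that the primary analysis has an inflated false-positive rate. It does not: the analysis section adjusts the p values and compares them with 0.05, which holds family-wise error at 0.05 whatever alpha the sample-size section prints. The fault is confined to the reported design figures.

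**What to change.** Keep the seven daily tests as planned. In Sample size {14}, give the per-day two-sided alpha as 0.05/7 = 0.0071, and print the standard deviation and control mean behind the 89 so that the calculation can be repeated. Then check which alpha was entered. If it was 0.00714, the 89 and the 80% stay as they are. If it was 0.01, restate per-day power as about 77% (76.6% with 89 evaluable per group, 77.2% with 90).

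The cost is a sentence or two in one section. No further enrolment is asked for, and neither the primary outcome nor the set of tests changes. The only downside is that the stated power may become slightly less favourable. Redefining the confirmatory tests as days 1 to 5 is not recommended: it would alter the primary analysis of a trial already recruiting, on a guess about where 0.01 came from.

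### The per-day alpha printed in the sample-size section (0.01) does not match Bonferroni over the seven daily primary tests (0.05/7 = 0.0071); if 0.01 was the value used, per-day power is about 77%, not 80%

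*Protocol article*

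**What the plan says.** Protocol article, Sample size {14}. The trial is sized on the child-reported overall pain score, to detect a 30% reduction "at any of the first 7 days of follow-up, and assuming the same SD on these days". The result is "we will need 89 subjects per group to achieve 80% power and a two-sided type-I error of 0.01 at each day", by two-sample t-test. The next sentence adds: "The type-I error rate is adjusted by Bonferroni correction for multiple comparisons". With 10% dropout the requirement becomes 99 per group, and 100 per group are planned. The SD is said to come from an earlier outpatient trial, but neither its value nor a control mean is printed.

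Protocol article, Statistical methods for primary and secondary outcomes {20a}, Aim 1. The same score "will be compared between the VR-PAT and control groups during each of the first 7 days of follow-up", again by two-sample t-test. The p values are "adjusted by Bonferroni correction to account for multiple comparisons and then compared to the critical value of 0.05".

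**The concern.** Both sections name seven days and both name Bonferroni, yet the one number that should connect them does not follow. Seven tests against a family-wise 0.05 give 0.0071 per test. A per-test level of 0.01 belongs to five tests, and nothing in the primary analysis has five comparisons. The eligibility criteria mention daily changes for about 5 days, but neither section ties the number of tests to that.

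Two things are at stake. First, the 80% power, the 89 evaluable and the 99 randomised per group may describe a more lenient test than the one the trial will run. Second, a daily p value between 0.0071 and 0.01 meets the level printed in the sample-size section but fails the rule in the analysis section. That is better settled before the primary analysis than after it.

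**Working it through.** **Inputs.** From Sample size {14}: 89 per group, 80% power, two-sided alpha 0.01 per day, 10% dropout, 100 per group planned. From Statistical methods {20a}: seven daily tests, family-wise level 0.05. The SD and control mean are not needed, because the standardised effect d can be solved from the article's own figures.

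**1. Threshold per day.** 0.05/7 = 0.00714. For comparison, 0.05/5 = 0.01.

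**2. The plan's own figures.** The dropout step reproduces: 89/0.9 = 98.9, so 99. The 89 itself cannot be rebuilt without a mean and SD, so d is solved from it. In the normal approximation

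d = (z for alpha/2 + z for power) × √(2/n) = (2.576 + 0.842) × √(2/89) = 0.512.

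With the noncentral t distribution, d = 0.517. Either value returns 89 at alpha 0.01 by construction.

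**3. Case A: 0.01 was used exactly.** Keep d and change alpha to 0.05/7, for which z = 2.690. Normal approximation with 89 per group: d√(n/2) = 0.512 × √44.5 = 3.417, and power = Φ(3.417 − 2.690) = Φ(0.727) = 76.6%. The noncentral t gives:

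| Evaluable per group | Power at alpha 0.01 | Power at alpha 0.05/7 |
|---|---|---|
| 89 | 80.0% | 76.6% |
| 90 (100 less 10%) | 80.5% | 77.2% |
| 96 | 83.5% | 80.5% |
| 100 (no dropout) | 85.3% | 82.5% |

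Allowing for 89 having been rounded up from just above 88 (d up to 0.520), power at 0.05/7 is at most 77.2% with 89 and 77.7% with 90. For 80% power, 95 to 96 evaluable per group are needed, which is 106 to 107 randomised after 10% dropout.

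With 90 evaluable, 80% power at 0.05/7 requires d = 0.532. With the SD held fixed, that is 30% × 0.532/0.517 = 30.9%, or about 31%.

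**4. Case B: 0.01 is 0.0071 rounded.** If 89 was obtained at 0.05/7, then d = 0.535. Power at 0.05/7 is 80.0% with 89 and 80.6% with 90. At a literal 0.01, the same d needs only 84 per group, so the printed alpha and the printed 89 would still not belong together.

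**The case against.** **Rounding.** The strongest reply is that 0.00714 printed to two decimals is 0.01. The sample-size section names seven days and Bonferroni and never mentions five tests, which fits that explanation. It cannot be excluded, because the inputs behind 89 are not printed. This stands, and it makes the loss of power conditional. It does not rescue the printed alpha: a reader who takes 0.01 literally cannot get from the plan's effect to 89.

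**Small consequence.** Even in case A the loss is about 3 percentage points, the detectable reduction moves from 30% to about 31%, and power exceeds 80% if nobody drops out. The SD also comes from another setting and a VAS rather than the NRS, and that uncertainty may well be larger. This stands too. It bears on how much the error matters, not on whether the figure is right.

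**Type-I error.** A reader might infer that seven tests at 0.01 allow a family-wise error of up to 7% (7 × 0.01). The article does not support that. Statistical methods {20a} sets the decision rule, and comparing Bonferroni-adjusted p values from seven tests with 0.05 holds the family-wise error at or below 5%. The 7% bound would arise only if someone took the threshold from the sample-size section instead.

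**Per-day power.** A reader might also take 77% as the chance that the trial shows an effect at all. It is the power on a single day, matching the article's own per-day statement. Power for at least one significant day is higher and depends on the between-day correlation, which the article does not give. In case A, with 89 per group and the same effect on all seven days, a normal-approximation simulation gives about 98% at an assumed correlation of 0.5 and about 88% at 0.9.

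**Conclusion.** Wrong as written. The per-day alpha in the sample-size section should read 0.05/7 = 0.0071, on the article's own count of seven tests and its own family-wise level of 0.05. That conclusion needs no assumption.

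The size of the power error depends on what was entered in the calculation. If 0.01 was entered, per-day power is 76.6% with 89 and 77.2% with 90 evaluable per group, against the stated 80%. If 0.0071 was entered, the 80% is correct and the fault is only in the reporting. A reader might infer that the stated power is simply false; without the control mean and SD, the article supports only the range from about 77% to 80%. The case A figures assume equal groups, the 10% dropout stated and the same SD on every day, as the article does. The planned test, its error control and the 200 participants are unaffected.

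**What to change.** 1. In Sample size {14}, replace 0.01 with a per-day two-sided alpha of 0.05/7 = 0.0071.
2. Confirm which alpha produced the 89, and print the control mean and SD used so that it can be reproduced.
3. If the alpha was 0.01, restate the power: 100 per group with 10% dropout gives about 77% on each day for a 30% reduction, or 80% for a reduction of about 31% with the SD held fixed. If it was 0.0071, keep the 80%.
4. Say that the power figure is per day.

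The cost is one paragraph of text and one look at the original calculation. No extra enrolment is needed and the analysis section can stay as it is. At worst the stated per-day power becomes about 3 points less favourable.

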### Recruitment {15}

Participants will be recruited after their first dressing change in the Outpatient Burn Clinic or at discharge from the ED or inpatient burn unit. Patients of age will be initially screened daily through the electronic medical record system at each hospital for general eligibility. Once the treating clinician assesses the burn wound and determines the type of dressing needed, trained research staff will approach patients receiving a daily dressing to assess their pain status and smartphone availability. Study introductions are made during this in-person visit, and informed consent/assent is obtained from interested caregivers and patients. No recruitment materials will be used to advertise the study.

## Assignment of interventions: allocation

### Sequence generation {16a}

A random-block randomization scheme with a block size of four will allocate participants to either intervention or control at a 1:1 ratio without stratification. Each site had its own randomization scheme stored in its respective Data Access Group in REDCap to ensure that subjects within each arm were distributed evenly between each site.

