### Concealment mechanism {16b}

Study participants are randomized into control and intervention groups after signing consent and completing the baseline survey. Research recruiters and subjects do not know the intervention assignment until the subject is randomized in REDCap.

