### Implementation {16c}

The project manager generated the allocation sequences and uploaded them to the Randomization Module in REDCap. The research study team involved in recruitment will screen and enroll subjects into the study and assign them to intervention groups by using the randomize button within REDCap, which only reveals the intervention group for the current participant. The clinical care team will determine the method of care required for the patient to confirm if the subject will qualify for daily dressing changes. These decisions will be made based on treatment needs without research influence.

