## Assignment of interventions: blinding

### Who will be blinded {17a}

We cannot blind the participants, caregivers, or research team from the assigned intervention since one group will use the VR headset and one will not. The study biostatistician will be blinded to the intervention group while performing analyses on the primary outcome. The data will be blinded by removing labels such as “VR” and “Control” and will be replaced with unidentifiable letters (i.e., “A” and “B”). The biostatistician will need to become unblinded for secondary outcomes as those in the intervention group will be the only ones answering the VR experience questions.

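### A fixed block size of four on a separate list per site could let unblinded recruiters deduce up to an expected third of allocations before approaching a family

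*Protocol article*

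**What the plan says.** Sequence generation {16a} gives one block size: "A random-block randomization scheme with a block size of four will allocate participants", "to either intervention or control at a 1:1 ratio without stratification". The same section keeps the two sites apart: "Each site had its own randomization scheme stored in its respective Data Access Group in REDCap". The scheme is called random-block, but only one size is given. The natural reading is therefore randomly permuted blocks of four, with two children per arm in each block.

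On who sees what, Who will be blinded {17a} says "We cannot blind the participants, caregivers, or research team from the assigned intervention". Implementation {16c} says "The research study team involved in recruitment will screen and enroll subjects into the study and assign them to intervention groups", using a REDCap button "which only reveals the intervention group for the current participant". Concealment mechanism {16b} concludes that "Research recruiters and subjects do not know the intervention assignment until the subject is randomized in REDCap", and places randomisation after consent and the baseline survey.

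On discretion at entry, Recruitment {15} says "trained research staff will approach patients receiving a daily dressing to assess their pain status and smartphone availability". Under Eligibility criteria {10} the child must report a pain score of at least 1 on the 0–10 scale from the most recent dressing change. Families without a VR-compatible smartphone are excluded.

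**The concern.** Concealment has two parts: the list must be hidden, and the next entry must not be deducible from earlier ones. The plan secures the first but not the second. In a block of four, once two children have gone to the same arm, the rest of the block is known. The fourth child's arm is always known. Earlier assignments are visible in routine work: headsets go to the intervention group at Visit 1 (Table 1), and intervention families get a check-in call the next business day (Plans to promote participant retention {18b}). With one list per site, only local assignments have to be remembered.

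Where the next arm is deducible, the assurance in Concealment mechanism {16b} fails before the family is approached. Staff could then, even without intent, vary which families they approach, or how they handle a borderline pain report or a doubtful phone. The phone criterion is a live one, because the Discussion reports app download problems and pauses in recruiting iPhone users.

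The outcome would be exposed to any such shift. The primary analysis in Statistical methods {20a} is an unadjusted two-sample t-test of child-reported pain on each day, in a trial where child and caregiver know the arm. A baseline difference created at enrolment would pass straight into that comparison.

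**Working it through.** The article gives no predictability figure, so there is none to reproduce.

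**Inputs.** Block size 4, ratio 1:1 and a separate list per site (Sequence generation {16a}). Total 200 children (Sample size {14}). Two sites and 48 months of recruitment (Study setting {9}, Participant timeline {13}).

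**Step 1: forced positions.** There are C(4,2) = 6 equally likely blocks. A position is forced when one arm has already been used twice in the block.

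| Block | Forced positions | Number |
|---|---|---|
| AABB | 3, 4 | 2 |
| BBAA | 3, 4 | 2 |
| ABAB | 4 | 1 |
| ABBA | 4 | 1 |
| BAAB | 4 | 1 |
| BABA | 4 | 1 |

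Forced share = (2×2 + 4×1) / (6×4) = 8/24 = 33.3%. Over the whole trial, 200 × 1/3 ≈ 67 children.

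**Step 2: best-guess rate.** The tracker guesses the arm with more places left in the block.

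- Position 1: 1/2.
- Position 2: 2/3, because two of the three remaining places belong to the other arm.
- Position 3: 1/3 × 1 + 2/3 × 1/2 = 2/3.
- Position 4: 1.

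The mean is (1/2 + 2/3 + 2/3 + 1)/4 = (17/6)/4 = 17/24 = 70.8%, against 50% under simple randomisation. The Blackwell–Hodges formula with n = 2 agrees: [n + (2^(2n)/C(2n,n) − 1)/2]/(2n) = [2 + (16/6 − 1)/2]/4 = 70.8%.

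**Step 3: how hard tracking is.** 200/48/2 ≈ 2.1 children per site per month, if the sites recruit equally (an assumption). A tracker needs to remember at most three earlier children, and where the block began.

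**Step 4: varying block sizes.** This was simulated with 1,500 runs of 100 allocations, each block size drawn with equal probability. The recruiter knows the set of sizes but not their order, and updates optimally after each assignment. The sets of sizes are illustrative and do not come from the article.

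| Block sizes | Known with certainty | Best guess right |
|---|---|---|
| 4 only (current) | 33.3% | 70.8% |
| 4, 6 | 5.5% | 69.2% |
| 2, 4, 6 | 4.2% | 70.1% |
| 4, 6, 8 | 2.2% | 67.9% |

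**Step 5: imbalance.** An unfinished block of size b leaves a difference of at most b/2. That is 2 per site now and 4 per site with a largest block of 8. If the change came mid-block, the old block could strand a difference of 2, giving 2 + 4 = 6.

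**The case against.** The strongest reply is that a third is a conditional figure. Nowhere does the article say that recruiters are told the block size, or that one person sees every assignment. Oversight and monitoring {5d} gives each site at least one coordinator, so there may be several. This stands, and it is why the figure is an upper bound. It is not fully reassuring, because the article itself prints the block size, with recruitment open and completion expected in April 2027.

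Opportunity and motive are also limited:

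- Children are screened daily from the medical record, and the clinical team chooses the dressing.
- Eligibility is tied to the first clinic dressing change or discharge, so staff could mostly lose a child, not defer one to another slot.
- Recruitment is slower than anticipated, so skipping a child is costly.
- Controls receive the headset at Visit 2, which weakens any wish to steer a child into the VR arm.
- Consent and baseline come before randomisation, which prevents exclusion once the arm is revealed on screen. It does not help where the arm was deduced earlier.

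A reader might infer that staff score the eligibility pain and could raise or lower it at will. The documents do not support that: the child reports it and staff collect it. With a cut-off of 1, only the boundary between 0 and 1 is open to handling. The larger remaining route is the choice of whom to approach.

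Statistical methods {20a} also has a mixed model that adjusts for confounders deemed unbalanced. It is not the primary analysis, and it can adjust only for what was measured.

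Finally, the remedy removes certainty but little of the guessing advantage. That is correct. Certain knowledge is nevertheless what most directly defeats concealment.

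**Conclusion.** The point holds as an avoidable weakness in concealment, and correcting it is a cheap improvement. With blocks of four on separate site lists and unblinded staff who both recruit and randomise, up to an expected third of allocations (8 of 24 positions, about 67 of 200) could be deduced before a family is approached, with a best-guess rate of 70.8%. This rests on two assumptions: recruiters know the block size, and they track earlier assignments at their site.

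A reader might go further and conclude that a third of allocations are in fact known, or that the arms are already unbalanced through selection. Neither follows. Nothing in the article shows tracking or selection, and no bias in the pain difference has been estimated. What is shown is that the statement in Concealment mechanism {16b} can fail under the scheme as described.

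**What to change.** For the unused slots at each site, upload a new REDCap allocation table with randomly varying block sizes, for example 4, 6 and 8. Start it at a block boundary and do not disclose the sizes to recruiting staff. Amend Sequence generation {16a} to say that block sizes vary at random and are withheld from recruiters, without listing them. Completed allocations stay as they are.

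**Gain:** certain knowledge falls from 33% to about 2%, even for a recruiter who knows the set of sizes; the best-guess rate falls only from 70.8% to about 68%.

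**Cost:** one new table per site and a short amendment. The possible end-of-list imbalance rises from 2 to 4 children per site, or to 6 if the switch is made mid-block. Only allocations after the change are protected. The article does not say how many remain, so the total benefit cannot be sized, and it shrinks with delay.
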